#### Secondary outcomes

Outcomes will be reported for the two groups as mean ± standard deviation for normally distributed variables and the median and interquartile range for nonparametric variables. The two groups will be compared using chi-square tests, two sample Student’s *t*-test or the Wilcoxon rank-sum test as appropriate. Time-to-event outcomes will be defined from the completion of surgery until the time of event. Patients who do not have the event at last follow-up will be censored. The number of censored events is expected to be low as both events (ambulation and bowel movements) are requirements prior to the patient’s discharge from hospital. Time to event outcomes will be analyzed using the Kaplan-Meier method and survival curves will be compared between the two groups using the log-rank test.Sample size calculation

Our pilot data consisted of 111 patients that had undergone liver resection surgery between April 2004 and January 2009 prior to the use of MOTAP catheters when postoperative pain relief was provided by IV PCA hydromorphone alone. Cumulative hydromorphone consumption over the first 48 hours after surgery was 39.09 ± 25.07 mg. Based on our experience with the use of MOTAP catheters following adult liver donation surgery, we have found a reduction of 47% in mean cumulative opioid consumption over the first 2 postoperative days (48 hours). Patients receiving MOTAP catheters consumed a mean ± SD of 20.81 ± 15.8 mg of hydromorphone. The difference of approximately 18 mg over 48 hours is clinically significant and represents a reduction of almost 50%.

To be conservative, we will estimate a relative reduction in mean cumulative opioid consumption of 40%. Assuming a baseline opioid consumption of 39.09 mg with a standard deviation of 25.07, a sample size of 58 patients per group will achieve 90% power at a significance level (alpha) of 0.05. We will round up to 120 patients in total (60 patients in each group).

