### Secondary objectives

To assess the effect of MOTAP catheters on:

1. Postoperative pain intensity.

2. Opioid-related adverse effects, including nausea, vomiting, pruritus, sedation, and postoperative ileus.

3. Time to ambulation, duration of hospital stay and reduced postoperative pain disability.

4. Post-surgical complications (for example, pneumonia).

5. Incidence and intensity of chronic postsurgical pain.

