### Recruitment

Patients meeting the eligibility criteria will be recruited at the preoperative surgical consent visit or the anaesthesia pre-assessment clinic. Information pamphlets will be provided and written informed consent will be obtained. At the time of enrolment, patients will complete baseline questionnaires: the ‘Preoperative Current Pain and Pain History Questionnaire’, Numeric Rating Scale (NRS)
[30] for Pain Intensity and Pain Unpleasantness, the Pain Catastrophizing Scale (PCS)
[31], the McGill Pain Questionnaire - Short Form-2 (SF-MPQ-2)
[32,33], and the Hospital Anxiety and Depression Scale (HADS)
[34].

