1. NRS
[30] scores for pain at rest and with coughing (0 = no pain, 10 = worst possible pain) three times daily (TID) for 48 hours and then daily until discharge.

2. Preoperative Current Pain and Pain History Questionnaire, NRS for Pain Intensity and Pain Unpleasantness, PCS
[31], SF-MPQ-2
[32,33], Pain Disability Index (PDI)
[36,37], and HADS
[34] at baseline.

3. NRS patient satisfaction scores regarding pain control (0 = totally satisfied, 10 = totally dissatisfied) TID for the first 48 hours and then daily until discharge.

4. NRS for Pain Intensity and Pain Unpleasantness, PCS
[31], SF-MPQ-2
[32,33], and HADS
[34] on the day of discharge.

5. Long-term pain Follow-Up Pain Questionnaire, PDI
[36,37], PCS
[31], SF-MPQ-2
[32,33], HADS
[34], and The Follow-Up Questionnaire 6 months following surgery (via a routine follow-up telephone call).

6. In-hospital opioid-related side effects - presence of nausea, vomiting, pruritus, and dizziness (assessed TID for the first 48 hours, then daily until discharge).

7. Sedation scores, measured TID for the first 48 hours, then daily until discharge using a standard sedation scale (0 = alert, 1 = mild (occasionally drowsy, easy to arouse), 2 = moderate (frequently drowsy, easy to arouse), 3 = severe (somnolent, difficult to arouse), S = normal sleep, easy to arouse).

8. Duration of hospital stay.

9. Time to first bowel movement.

10. Time to ambulation.

11. Incidence of in-hospital complications, graded using the Clavien classification
[38].

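### The secondary analysis as stated makes no use of baseline scores the trial collects, and the two baseline lists disagree on the Pain Disability Index

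*Protocol article*

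**What the plan says.** Analysis. In the protocol article, Data analysis, Secondary outcomes, the reporting rule is "Outcomes will be reported for the two groups as mean ± standard deviation for normally distributed variables", with median and interquartile range otherwise. The comparison rule follows: "The two groups will be compared using chi-square tests, two sample Student’s *t*-test or the Wilcoxon rank-sum test as appropriate". Time-to-event outcomes get Kaplan-Meier curves and a log-rank test. No covariate, change score or repeated-measures model is named.

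Schedule. Under Outcome assessment, Secondary outcomes:
- Item 2 (baseline): pain history questionnaire, NRS intensity and unpleasantness, PCS, SF-MPQ-2, PDI and HADS. The PDI entry reads "Pain Disability Index (PDI".
- Item 4 (discharge): NRS intensity and unpleasantness, PCS, SF-MPQ-2 and HADS.
- Item 5 (6 months, by telephone): begins "Long-term pain Follow-Up Pain Questionnaire, PDI" and goes on to PCS, SF-MPQ-2, HADS and a follow-up questionnaire.

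The Recruitment section has its own baseline list, introduced by "At the time of enrolment, patients will complete baseline questionnaires". It names the pain history questionnaire, NRS intensity and unpleasantness, PCS, SF-MPQ-2 and HADS. PDI is not on it.

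One line of the Secondary objectives reads "Time to ambulation, duration of hospital stay and reduced postoperative pain disability". PDI is the only instrument in the article that is named as a disability measure.

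**The concern.** There are two linked matters.

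First, patients complete several questionnaires before surgery that are repeated later, and the stated tests compare the groups without reference to the earlier score. When a baseline score predicts the later one, leaving it out widens the interval and lets a chance difference between the groups at baseline pass into the estimate. The sample size was set on opioid consumption alone, so the questionnaires have whatever precision 60 per group happens to give.

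Second, the two baseline lists conflict within the current text. If the Recruitment list were followed, a patient would have a 6-month PDI and nothing earlier, since PDI is not in the discharge set either. The trial is already enrolling (Trial status), and a preoperative score that was not taken cannot be obtained later.

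**Working it through.** **Plan's own figure.** The article states no figure for the questionnaires. Its one calculation is for the primary endpoint: a 40% reduction from 39.09 mg is 0.40 × 39.09 = 15.64 mg, with SD 25.07, two-sided alpha 0.05 and 90% power. A t-test calculation gives just over 55.0, so 56 per group, against the stated 58. Power at 58 per group is 91.5%. The figure is reproduced to within two patients and is not in question here. The primary endpoint has no baseline value.

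**Which scores have a baseline and a repeat**

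| Instrument | Recruitment list | Item 2, baseline | Item 4, discharge | Item 5, 6 months |
|---|---|---|---|---|
| NRS intensity, unpleasantness | yes | yes | yes | no |
| PCS | yes | yes | yes | yes |
| SF-MPQ-2 | yes | yes | yes | yes |
| HADS | yes | yes | yes | yes |
| PDI | **no** | **yes** | no | yes |

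The lists conflict in the PDI row only.

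**What baseline adjustment is worth.** Let r be the correlation between the baseline and follow-up score. The article does not give it, so a range is shown. Relative to comparing follow-up scores alone (variance 1):
- ANCOVA: variance factor 1 − r²
- Change score: variance factor 2(1 − r)

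With n = 60 per group, all observed, and a normal approximation, the follow-up-only comparison has 80% power for a difference of (1.960 + 0.842) × √(2/60) = 0.511 SD. The power of ANCOVA for that same difference is Φ(2.802/√(1 − r²) − 1.960). The follow-up-only sample size that would match ANCOVA is 60/(1 − r²).

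| r (assumed) | ANCOVA variance | Saving | ANCOVA power at 0.511 SD | Matching n per group, follow-up only |
|---|---|---|---|---|
| 0.1 | 0.99 | 1% | 80.4% | 61 |
| 0.2 | 0.96 | 4% | 81.6% | 63 |
| 0.3 | 0.91 | 9% | 83.6% | 66 |
| 0.5 | 0.75 | 25% | 89.9% | 80 |
| 0.6 | 0.64 | 36% | 93.8% | 94 |

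A t-test on change scores does not do the same job. Its variance factor is 1.40 at r = 0.3 (power 65.8%, worse than ignoring baseline) and 1.00 at r = 0.5 (power 80.0%, no gain). It is never better than ANCOVA, because 2(1 − r) − (1 − r²) = (1 − r)², which is not negative.

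**Where r may lie.** Table 1 excludes chronic pain disorders and long-term opioid use. Preoperative pain and disability scores may therefore cluster near the floor, which would put r for SF-MPQ-2 and PDI toward the top rows. That argument bears less on PCS and HADS, which measure catastrophizing, anxiety and depression.

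**The case against.** The strongest reply is that the stated method is valid. Under randomization an unadjusted comparison of follow-up scores is unbiased, and the choice of covariates is often left to an analysis plan, which is not shown here. The qualifier on the tests does not say whether the tested variable is the raw score or the change. This stands in part. An unseen plan could specify ANCOVA. But the article does not leave the method blank: it names the tests, none takes a covariate, and the change-score reading would be less efficient than ANCOVA.

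Second, the gain rests wholly on an assumed r and could be as small as 1% to 4%. That is correct, and no single figure from the table should be read as a property of this trial.

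Third, the PDI mismatch may be only editorial. The outcome list is explicit, the Recruitment paragraph does not claim to be complete, and nothing shows that a site works from it. A reader might infer that sites are failing to collect baseline PDI; the article does not show that. It shows two lists that disagree.

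A reader might also infer that a 6-month PDI without a baseline cannot be interpreted. It can: the randomized comparison between groups remains valid. What is lost is adjustment and the description of change within patients, and the chronic-pain exclusion makes substantial disability at entry less likely.

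Nor do all these scores carry the chronic-pain and disability objectives. The Secondary objectives mention neither catastrophizing nor anxiety and depression, so PCS and HADS serve no named objective. The incidence of chronic pain is a proportion, for which chi-square is suitable.

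**Conclusion.** The point holds as a low-cost improvement plus a small contradiction, both confined to secondary outcomes. The stated tests do not use baseline scores that the trial asks patients to provide. The cost is in precision and protection against chance imbalance, with no bias. The variance saving forgone is 1 − (1 − r²) = r², from about 1% at r = 0.1 to 36% at r = 0.6. It rests on an assumed r, and the power figures also assume all 60 per group are observed. Loss to follow-up at 6 months would lower them.

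The PDI conflict is certain on the text. Its consequence is conditional: only patients enrolled under the shorter list would lack a baseline PDI, and for them the loss cannot be undone.

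**What to change.** 1. In Data analysis, Secondary outcomes, state that the continuous scores with a baseline (NRS intensity and unpleasantness, PCS, SF-MPQ-2, HADS, PDI) are compared at each later time by ANCOVA on treatment, the same score at baseline, and centre, the stratification factor. Use robust standard errors or a rank-based check for skewed scores. Keep chi-square for incidence outcomes and the log-rank test for time to event.
2. Add PDI to the enrolment questionnaires in the Recruitment section so that it matches item 2 of the outcome list.
3. State how a missing baseline PDI is handled for patients already enrolled, for example by imputing the overall baseline mean or by a missing-value indicator. Their 6-month values then stay in the between-group comparison, with less precision.

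The cost is a sentence or two in the analysis text and one entry in the Recruitment list, for a questionnaire that the outcome list already requires. No added patients or visits are needed. The change cannot recover a baseline PDI that was not taken, so the lists should be reconciled while enrolment continues.

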### Criteria for removal from study

If, at any time, the patient is found to be ineligible for the protocol as designated in the section on eligibility the patient will be removed from the study. Patients who are not extubated within 4 hours from the end of the operation or who are reintubated within 48 hours from the end of the operation (including a return to the operating room) will also be excluded from the primary analysis, although we will continue to follow them while in hospital. Patients who wish to withdraw from the study at any point in time will be able to do so.

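### Censoring patients who die before walking or moving their bowels makes the Kaplan-Meier curves overstate recovery in any arm with such deaths

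*Protocol article*

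**What the plan says.** The protocol article, under Data analysis, Secondary outcomes, sets the rule for the time-to-event outcomes in four steps.

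- Time origin: "Time-to-event outcomes will be defined from the completion of surgery until the time of event".
- Censoring: "Patients who do not have the event at last follow-up will be censored". No exception is made for death.
- Expected extent: "The number of censored events is expected to be low as both events (ambulation and bowel movements) are requirements prior" to discharge.
- Analysis: "Time to event outcomes will be analyzed using the Kaplan-Meier method", with the curves compared by log-rank.

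The two outcomes covered are time to ambulation and time to first bowel movement. The Criteria for removal from study allow withdrawal at any time. They take patients with late extubation or reintubation out of the primary analysis, "although we will continue to follow them while in hospital". As written, that exclusion does not reach the secondary outcomes.

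**The concern.** Kaplan-Meier reads as a recovery probability only if a censored patient would have gone on to recover at the same rate as those still under observation. The article's own reason for expecting little censoring shows who the censored patients will be. If ambulation and a bowel movement are required before discharge, everyone discharged has both events. What remains is mainly in-hospital death before the event, and withdrawal. A patient who has died cannot recover, yet the rule drops that patient from the risk set and lets the others stand in. Expecting few such patients limits the size of the error but does not make the censoring uninformative.

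At stake is the reading of two functional-recovery outcomes: ambulation, named in the third secondary objective, and bowel function, which bears on ileus in the second. If deaths differ between arms, the curve for the arm with more of them is too favourable.

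**Working it through.** **Inputs.** From the article: 60 patients per group, two-sided 0.05, and the censoring rule, Kaplan-Meier and log-rank as above. The article gives no figure for deaths or recovery times, so these are assumptions: 0 to 5 deaths before the event in one arm, none in the other.

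**The plan's own figure.** The only computed design figure is the sample size for opioid consumption. It does not bear on this point, but it is sound. The difference is 0.40 × 39.09 = 15.64 mg with SD 25.07. A two-sample t-test at 90% power needs 55.002, so 56 per group. Dividing by the Wilcoxon efficiency, 55.002 / (3/π) = 57.6, gives the stated 58.

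**Step 1: exact arithmetic.** Suppose k of 60 patients die before the event and all the others recover, the last observation being a recovery. The estimated proportion not yet recovered is the product of (1 − 1/n) over the recovery times, where n is the number still at risk. At the last recovery n = 1, so the product is 0 and the curve ends at 100% recovered, whatever k is. The proportion that actually recovered is (60 − k)/60:

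| Deaths k | Curve ends at | Actually recovered |
|---|---|---|
| 1 | 100% | 59/60 = 98.3% |
| 2 | 100% | 58/60 = 96.7% |
| 3 | 100% | 57/60 = 95.0% |
| 5 | 100% | 55/60 = 91.7% |

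**Step 2: simulation.** There are 60 per arm with the same true recovery in both: log-normal time to event, median 4 days, log-SD 0.5. The k deaths fall in one arm, each at a uniform 25% to 100% of that patient's would-be event time. Two cases are run: the patients who die are the slowest recoverers, or they are picked at random. Censoring at death is compared with keeping the patient at risk to day 30 as never recovered. There were 1,500 replicates per row.

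Apparent 7-day recovery in the arm with deaths:

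| k | Who dies | Death censored | Death = not recovered | Excess (points) | Other arm |
|---|---|---|---|---|---|
| 1 | slowest | 87.4% | 87.0% | 0.4 | 86.9% |
| 2 | slowest | 87.7% | 86.7% | 1.0 | 86.9% |
| 3 | slowest | 88.6% | 86.9% | 1.7 | 87.0% |
| 5 | slowest | 90.3% | 86.6% | 3.7 | 86.8% |
| 1 | random | 86.6% | 85.3% | 1.3 | 86.8% |
| 2 | random | 86.4% | 83.9% | 2.5 | 86.9% |
| 3 | random | 86.2% | 82.5% | 3.7 | 86.9% |
| 5 | random | 85.8% | 79.5% | 6.3 | 86.9% |

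The curve is too high in every row, whoever dies.

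Mean log-rank Z (positive means the arm with deaths looks faster), and the chance that it is significantly faster when death is censored:

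| k | Who dies | Z, censored | Z, never recovered | Significantly faster, censored |
|---|---|---|---|---|
| 1 | slowest | +0.13 | −0.12 | 4.6% |
| 2 | slowest | +0.23 | −0.24 | 4.1% |
| 3 | slowest | +0.25 | −0.41 | 5.3% |
| 5 | slowest | +0.37 | −0.67 | 5.9% |
| 1 | random | −0.03 | −0.40 | 2.3% |
| 2 | random | −0.10 | −0.76 | 1.5% |
| 3 | random | −0.15 | −1.06 | 1.7% |
| 5 | random | −0.23 | −1.57 | 1.5% |

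With no deaths the two runs gave mean Z of +0.02 and −0.06 and significance rates of 3.0% and 2.3%, which shows the simulation noise. The two ways of handling death then agree exactly.

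**The case against.** Four points can be made for the plan as written.

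- **A log-rank test that censors deaths is a recognised analysis.** It compares the rate of recovery among patients still alive and at risk. Gray's test answers a different question. This stands: choosing one test over the other is partly preference. It does not rescue the Kaplan-Meier curve as an estimate of the proportion recovering.
- **Few patients are affected.** Only a death before the first ambulation or first bowel movement is mishandled; a later death already has its event. This stands and keeps the effect small.
- **These are secondary outcomes.** The primary endpoint, 48-hour opioid consumption, and the sample size are untouched. This stands.
- **An article is condensed.** Here, however, it states a censoring rule, gives a reason for it and names the analysis, so the point concerns stated text and not an omission.

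Two stronger readings are tempting, and the documents do not support them. A reader might infer that an in-hospital death counts as a short stay. The outcome list says only "Duration of hospital stay". It gives no end point and no rule for deaths, and the article names no test for stay beyond a general list ending "or the Wilcoxon rank-sum test as appropriate". A full protocol or analysis plan may settle this. A reader might also infer that the arm with more deaths will generally look faster. On the log-rank test it does so only if those who die would have been slow recoverers. In the simulation with randomly chosen deaths it did not.

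**Conclusion.** The point holds for the two time-to-event outcomes. The stated rule censors deaths before ambulation or first bowel movement, and the Kaplan-Meier curve then overstates recovery in an arm with such deaths. Under the assumed recovery times, the overstatement at 7 days runs from 0.4 points (one death among the slowest recoverers) to 6.3 points (five deaths at random) with 60 per arm.

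The effect on the test is conditional and small. If the patients who die are the slowest recoverers, the chance of a falsely significant faster recovery is about 4% to 6%, against roughly 2.5% with no deaths. If deaths are unrelated to recovery speed, that chance does not rise.

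The number of deaths, their placement in one arm and the recovery times are all assumptions, because the documents give none of them. This is a cheap improvement to two secondary outcomes and no threat to the trial's main conclusion.

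**What to change.** Replace the censoring sentence with wording such as: *A patient who dies in hospital before the event is counted as never having the event; only patients who withdraw are censored, at the time of withdrawal.* Then name one of two ways to carry it out:

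- treat death as a competing event, show the groups by cumulative incidence and compare them by Gray's test; or
- keep the patient in the risk set to the longest observed time and retain the log-rank test.

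Either is acceptable. If the sponsor prefers the log-rank test with deaths censored, the text should say that it compares recovery rates among patients still at risk, and cumulative incidence curves should still be shown. If a fuller plan already has a rule for deaths, the published text should be brought into line with it.

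The change costs a sentence or two and a few lines of code, and needs no new data. The small downside is that the figures become cumulative incidence curves in place of Kaplan-Meier curves. The choice should be fixed before the randomization code is released, so that it cannot depend on where the deaths fell.

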## Discussion

Data from this study will help us optimize postoperative pain management in patients undergoing liver resection. It will assist us in developing a standardized protocol for pain management for these operations. Based on the results of this work, we hope to further test the efficacy of these catheters in other surgical cohorts in which upper abdominal incisions are used and where central neuraxial blocks are either contraindicated or refused by the patient. Better control of pain will help improve patient’s pain experience, mobilization and physiotherapy following surgery, reduce pain disability and possibly decrease the incidence and intensity of CPSP.

## Trial status

This trial has been approved by the ethics boards at participating centres and is currently enrolling patients. Data collection will be completed by the end of 2014 with analysis mid-2015 and publication by the end of 2015.

### Ethics approval

Toronto Academic Health Sciences Network Research Ethics Boards from Sunnybrook Health Sciences Centre and from the University Health Network.

## Abbreviations

CPSP: chronic postsurgical pain; HADS: Hospital Anxiety and Depression Scale; IV PCA: intravenous, patient-controlled analgesia; MOTAP: medial open transversus abdominis plane; NRS: Numeric Rating Scale; PCA: patient-controlled analgesia; PCS: Pain Catastrophizing Scale; PDI: Pain Disability Index; SF-MPQ-2: McGill Pain Questionnaire - Short Form-2; TAP: transversus abdominis plane; TID: three times daily.
